## Abstract

**Background:**

Total hip arthroplasty is an effective surgical procedure commonly used worldwide for patients suffering the disabling effects of osteoarthritis when medical therapy is unsuccessful. Traditionally pre- and postoperative information for patients undergoing a hip arthroplasty has been provided by paper-based methods. Electronic health (eHealth) programs to support individualized patient education on preoperative preparation, in-patient care, and home rehabilitation have the potential to increase patient engagement, enhance patient recovery, and reduce potential postoperative complications.

**Objective:**

The aim of this study is to compare the addition of an eHealth program versus standard care for pre- and postoperative education on patient outcomes for primary total hip arthroplasty.

**Methods:**

One hundred patients undergoing a primary elective total hip arthroplasty will be recruited from a metropolitan hospital in Western Australia to participate in a 6-month parallel randomized control trial. Participants will be randomized to either the standard care group (n=50) and will be given the education booklet and enrolled to attend a 1-hour education session, or the intervention group (n=50), and will receive the same as the standard care plus access to an eHealth program titled “My Hip Journey.” The eHealth program encourages the patient to log in daily, from 2 weeks prior to surgery to 30 days postsurgery. The information on the platform will be aligned with the patient's individual surgical journey and will include exercises to be completed each day for the duration of the program. The primary outcome measure is the Hip Dysfunction and Osteoarthritis Outcome Score, version LK 2.0. Secondary outcome measures include the EuroQoL EQ-5D-5L, a 5-level 5-dimension quality of life measure, and the Self-Efficacy for Managing Chronic Disease Scale. Data will be collected at pre-admission (presurgery) and at 6 weeks, 3 months, and 6 months postsurgery. A patient satisfaction survey will be completed 6 weeks postsurgery and Web-based analytics will be collected 6 months postsurgery. A cost-effectiveness analysis, using the intention-to-treat principle, will be conducted from the hospital’s perspective.

**Results:**

Enrollment in the study commenced in January 2018 with recruitment due for completion towards the end of the year. The first results are expected to be submitted for publication in 2019.

**Conclusions:**

The outcomes and cost of using an eHealth program to support a patient’s recovery from a hip arthroplasty will be compared with standard care in this study. If the eHealth program is found to be effective, further implementation across clinical practice could lead to improvement in patient outcomes and other surgical areas could be incorporated.

**Trial Registration:**

Australian New Zealand Clinical Trials Registry (ANZCTR) ACTRN12617001433392; https://www.anzctr.org.au/Trial/Registration/TrialReview.aspx?id=373657&isReview=true (Archived by WebCite at http://www.webcitation.org/6yzoTuggx).

**Registered Report Identifier:**

RR1-10.2196/9654

An alternative forum for delivering patient education is through electronic health (eHealth). The World Health Organization defines eHealth as “the use of information and communication technologies for health” [11]. The introduction of eHealth programs to support individualized patient care at the pre-operative, peri-operative, and postoperative stages has the potential to improve patient engagement, self-care, and outcomes across the surgical pathway [12]. The implementation of eHealth programs enables a single source of credible information, which can be constantly updated as new information arises, and is accessible to all patients irrespective of geographical location. Programs can be individually tailored to the patient, provide a platform for communication with health care professionals, provide electronic reminders to prompt patients, and can be used by other health professionals and carers to provide an enhanced continuity of care [12].

The aim of this study is to compare the addition of an eHealth program versus standard care for pre- and postoperative education on patient outcomes for primary THA. The hypothesis is patients who have access to the eHealth program will have better physical functioning post-THA compared to patients receiving standard care.

## Methods

A prospective randomized controlled trial (RCT) will be conducted comparing an eHealth program to standard care for THA. Ethics approval was obtained from the participating study site (HPH505) and the University where the researchers are employed (19065).

### Study Duration

Recruitment of the trial began in January 2018 and data collection is due to be completed within 12 months.

### Setting

The setting of this study is a private metropolitan hospital in Western Australia with a focus on orthopedic surgeries. In 2017, there were a total of 848 hip surgeries performed in the hospital by 24 orthopedic surgeons. As the hospital is a private hospital, the surgeries are mostly funded through patients’ private insurance.

### Patients

Patients undergoing a primary elective THA will be invited to take part in the RCT. Patients will be screened and recruited during the usual pre-admission phone call conducted by the pre-admission nurse. Inclusion criteria are as follows: (1) the patient is undergoing a primary elective THA, (2) the patient is able to provide informed consent, (3) the patient is aged 18 years or over, and (4) there is a minimum lead-up time of three weeks prior to surgery. Exclusion criteria include the following: (1) the patient is undergoing a THA revision, (2) a bilateral THA, or (3) THA following a fractured neck of femur, (4) had a previous THA, (5) unable to converse in written or spoken English, (6) has no access to a Web-based device, and (7) has a risk assessment and prediction tool (RAPT) score less than six. The RAPT uses pre-operative patient factors of age, gender, pre-operative ambulatory distance, use of gait aid, community support, and presence of a home caregiver to predict their need for extended care after a THA [13].

### Randomization

One hundred patients will be randomized with a one-to-one treatment allocation to the intervention (n=50) or standard care (n=50) group at the time of consent. Allocation concealment in the order of recruitment will be conducted “off-site” after consent has been obtained. Permuted block randomization will be conducted to ensure an equal number of participants are allocated to each group per week. This will be conducted in weekly blocks of 10. Due to the nature of the research, blinding will not be possible for either the participants or the health care team. The researcher conducting the data analysis, however, will be blinded.

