### Intervention

The intervention for the trial is standard care as described above plus the addition of the eHealth education program. The eHealth program was developed specifically for patients undergoing a THA by a multidisciplinary team of clinicians, researchers, and consumer representatives. It provides information about the care requirements during the journey of a hip replacement, advice on well-being, and an exercise program. The information in the eHealth education program is for patients, support persons, relatives, and community health professionals and gives information on what to expect pre-operatively, whilst in hospital, postoperatively, and postdischarge.

Participants will access the eHealth program via a weblink after registration using a username and password. The program is designed to give participants continual access to information, at a time that suits them without them having to come to the hospital. It is recommended that participants use the program on a daily basis starting 2 weeks prior to surgery until 30 days postsurgery. However, the participants may have access to the program up to 4 weeks pre-operatively and will continue to have access until 12 months postsurgery. The eHealth program provides a suite of educational resources including fact sheets, videos, exercise videos, and email reminders about the pre- and postoperative care of a hip replacement. The resources are linked to the participants’ journey with a focus on personal wellbeing and its importance in the pre-operative and postoperative periods. Some examples of the resources included in the eHealth program are preparation for surgery, nutrition, pre- and postoperative exercise regimes, and medication management with additional information provided on walking aids and safety if living with pets. Each day, when the participant logs into their “My Program” window, it will display a list of videos and information as well as exercises that have been allocated for them to view or complete that day (Figure 1).

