### Outcome Assessment

Outcome measures will be collected at four time points, namely at pre-admission, 6 weeks, 3 months and 6 months after the surgery. Figure 2 presents a flow chart of the recruitment and trial participation process and Table 1 outlines the outcome assessments used in this study, as well as the collection time points for the assessments. Participants will be asked to complete the relevant assessments online and an email reminder will be sent to each participant when the assessment is due, followed by a reminder one week later.

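### Allocation is tied to consent, not to a completed baseline, so the self-reported pre-admission HOOS can be answered with the arm already known

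*Protocol article*

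**What the plan says.** All references are to the protocol article.

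- **Patients:** patients are "screened and recruited during the usual pre-admission phone call". At least three weeks must remain before surgery.
- **Randomization:** allocation is one to one, "to the intervention (n=50) or standard care (n=50) group at the time of consent". The next step reads "Allocation concealment in the order of recruitment will be conducted “off-site” after consent has been obtained". The same section states that "blinding will not be possible for either the participants or the health care team".
- **Outcome Assessment:** "Outcome measures will be collected at four time points, namely at pre-admission, 6 weeks, 3 months and 6 months after the surgery". On mode, "Participants will be asked to complete the relevant assessments online and an email reminder will be sent to each participant" when an assessment falls due, with a second reminder after a week. Table 1 places HOOS, EQ-5D-5L and SEMCD at pre-admission.
- **Intervention:** daily use is recommended from two weeks before surgery, but "the participants may have access to the program up to 4 weeks pre-operatively". The content includes pre-operative exercise.
- **Statistical Analysis:** the treatment effect is calculated from before to after the intervention, at 6 weeks. The primary outcome is assessed by analysis of covariance. Baseline HOOS is not among the named covariates. Changes are also compared with t tests and nonparametric tests.

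**The concern.** A baseline value protects a randomized comparison only if allocation cannot have influenced it. Here allocation follows consent, the participant is not blinded, and the instrument is a self-report completed online over a period that may extend to the one-week reminder. A patient who knows the arm may rate the hip, health or confidence differently. A patient with early login may also have begun the exercises or read the material.

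Any such shift enters the treatment effect directly, because the effect is defined on pre-to-post outcomes. The secondary outcomes share the exposure: SEMCD asks about confidence, which an education program could plausibly move, and the economic evaluation uses changes in HOOS and quality of life from the same baseline. Patients who learn their arm and never return baseline have no change score, so loss could differ by arm. Blinding the analyst, which the article does provide, does not address any of this.

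**Working it through.** **1. Order of events.** The stated sequence is call, consent, off-site allocation. Outcome Assessment supplies a label (pre-admission) and a mode (online, with reminders). It gives no order relative to allocation. Two sequences therefore fit the text: baseline completed around the call before allocation is released, or baseline completed online after it. Nothing shown excludes the second.

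**2. Can program use precede baseline?** Let L be the days from consent to surgery. Assume the baseline email goes out on the day of consent and access opens as early as the Intervention section allows.

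- Access opens min(L, 28) days before surgery.
- The one-week reminder falls L − 7 days before surgery.
- Days of access before the reminder = max(0, min(L, 28) − (L − 7)).

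| L | Access opens | Reminder | Days of access before reminder |
|---|---|---|---|
| 21 | day −21 | day −14 | 7 |
| 28 | day −28 | day −21 | 7 |
| 35 | day −28 | day −28 | 0 |

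Prior use is possible at short lead-up times and need not occur at longer ones. Knowledge of the arm is possible at every lead-up time.

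**3. The plan's own figure.** 42 / (1 − 0.15) = 49.4, rounded up to 50 per group, which matches the Sample Size section. The 42 cannot be checked because the difference and SD are not printed. Back-solving with 90% power and an assumed two-sided 5% level:

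d = (1.960 + 1.282) × √(2/42) = 0.707 SD (0.716 with the t distribution).

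**4. Size of the bias.** For a shift x in one arm's baseline:

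- change score: bias = −x
- baseline-adjusted analysis: bias = −b·x, where b is the slope of the outcome on baseline.

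The shifts and b = 0.3 are assumptions. The table takes a shift towards a better baseline in the intervention arm, with 42 evaluable per group and shifts measured in the design SD.

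| Shift (SD) | Change score: effect left; bias as share of 0.707; power | b = 0.3: effect left; bias as share of 0.707; power |
|---|---|---|
| 0.1 | 0.607; 14%; 80% | 0.677; 4%; 87% |
| 0.2 | 0.507; 28%; 64% | 0.647; 8%; 84% |
| 0.3 | 0.407; 42%; 46% | 0.617; 13%; 81% |

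A shift in the other direction would inflate the effect by the same amounts.

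**The case against.** The strongest reply is that the point rests on an absence. The flow chart is where the order of consent, baseline and randomization would normally be drawn, and it is not shown. A condensed article may also leave the order of steps on the day of recruitment to the full protocol. This stands against any claim that the order is wrong. It does not remove the point, because the article states a timing rule for allocation, and that rule makes consent, not a completed baseline, the condition.

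Three stronger readings are tempting, and the document supports none of them.

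- *A reader might infer that baseline is in fact collected after randomization, through an emailed link.* The article says online completion with email reminders; the only weblink described is the program's. Recruitment and baseline share the pre-admission label, so a baseline at the call also fits. The reminder rule is general and is not set out for baseline separately.
- *A reader might infer that intervention patients will have used the program before baseline.* That needs an early login and a late response. Recommended use starts two weeks before surgery, and access before then is only permitted. A prompt baseline precedes recommended use.
- *A reader might infer that more than a quarter of the design effect is at risk.* The 28% belongs to one assumed shift of 0.2 SD in a raw change score. With baseline adjustment at a slope of 0.3 the same shift gives about 8%. The article names analysis of covariance but does not list baseline HOOS as a covariate, so which multiplier applies is open. The ratio also assumes that the unprinted design SD is on the same scale as baseline HOOS.

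**Conclusion.** The point holds as a weakness in the stated procedure: it allows an unblinded, self-reported baseline to be completed after allocation. It does not show that this happens. Knowledge of the arm is possible from consent onward. Exposure to the program before baseline is possible only if login is issued early, and is most plausible at lead-up times of three to four weeks.

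Neither size nor direction of bias can be derived from the document. On the assumed shifts of 0.1 to 0.3 SD, the bias is about 14% to 42% of the implied 0.71 SD effect for change scores and about 4% to 13% with an assumed baseline slope of 0.3. The 0.71 SD itself assumes a two-sided 5% test. The order should be corrected in the protocol, since the remedy is specific and leaves 50 per group unchanged. If the trial already collects baseline first, one sentence saying so resolves it.

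**What to change.** Amend the Randomization section so that the order is: consent; baseline HOOS, EQ-5D-5L and SEMCD submitted; off-site allocation requested and disclosed; eHealth login issued to the intervention arm. State the same order under Outcome Assessment.

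Recruitment began in January 2018, so some patients may already be enrolled. For them, compare the time stamp of baseline submission with those of allocation and first login, flag baselines completed after either, report the counts by arm, and run a sensitivity analysis without the flagged records.

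**Cost.** Sample size does not change. Allocation may be delayed by up to about a week if patients wait for the reminder. At the minimum lead-up the margin before recommended daily use is 21 − 14 = 7 days, so a late responder can use all of it. Delayed allocation also has to be fitted to the weekly blocks of 10. A few patients who consent but do not complete baseline will not be randomized.

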### Standard Care

The comparator for the trial, namely standard care, is an Enhanced Recovery Program based on an orthopedic recovery program established in The United Kingdom [14]. It consists of participants receiving paper-based information, attending a 1-hour hospital-based face-to-face pre-operative education session, and a postdischarge follow-up phone call. The education session is presented by a registered nurse, occupational therapist, pharmacist, and physiotherapist and participants are encouraged to bring their support person to the session. Examples of the content in the paper-based information and education session include fall prevention, wound care, showering, healthy eating, returning to work, pain management, and selecting a personal alarm. The postdischarge phone call is conducted within one week of discharge by a registered nurse from the ward. During the phone call the nurse will ask specific questions about how the patient is coping postdischarge, including questions about pain management, wound healing, exercise and mobility, nutrition and hydration, bowel management, and how well the patient is managing daily living activities.

### Intervention

The intervention for the trial is standard care as described above plus the addition of the eHealth education program. The eHealth program was developed specifically for patients undergoing a THA by a multidisciplinary team of clinicians, researchers, and consumer representatives. It provides information about the care requirements during the journey of a hip replacement, advice on well-being, and an exercise program. The information in the eHealth education program is for patients, support persons, relatives, and community health professionals and gives information on what to expect pre-operatively, whilst in hospital, postoperatively, and postdischarge.

Participants will access the eHealth program via a weblink after registration using a username and password. The program is designed to give participants continual access to information, at a time that suits them without them having to come to the hospital. It is recommended that participants use the program on a daily basis starting 2 weeks prior to surgery until 30 days postsurgery. However, the participants may have access to the program up to 4 weeks pre-operatively and will continue to have access until 12 months postsurgery. The eHealth program provides a suite of educational resources including fact sheets, videos, exercise videos, and email reminders about the pre- and postoperative care of a hip replacement. The resources are linked to the participants’ journey with a focus on personal wellbeing and its importance in the pre-operative and postoperative periods. Some examples of the resources included in the eHealth program are preparation for surgery, nutrition, pre- and postoperative exercise regimes, and medication management with additional information provided on walking aids and safety if living with pets. Each day, when the participant logs into their “My Program” window, it will display a list of videos and information as well as exercises that have been allocated for them to view or complete that day (Figure 1).

**Figure 1 figure1:**
[figure not shown]
Screenshot example of patient’s “My Program” for one week.

Each exercise is allocated a specific number of repetitions and sets that the participant is required to perform, and this information is included with the information about the exercise for the participant. Participants have access to the health care team via the program’s email for 4 weeks postdischarge and can invite their regular health care providers (such as their community occupational therapist and physiotherapist) or support person to be part of the program. The health professional team at the hospital can personalize the participant’s program including the exercises by editing in number of sets and repetitions recommended for each exercise.

Intervention fidelity will be assessed using analytics built into the website. After a participant watches a video or reads information, they will be prompted rate it. The program will then mark it as read and record information about how long the participant spent on that piece of information. In addition, after the exercise videos are completed by the participant, they will be prompted to mark them as complete. Automatically generated emails from within the program are sent on a regular basis to inform participants of the information available on the platform and provide instructions pre- and postoperatively. The health care team have access to the platform and can view the website analytics for each participant.

### Outcome Assessment

Outcome measures will be collected at four time points, namely at pre-admission, 6 weeks, 3 months and 6 months after the surgery. Figure 2 presents a flow chart of the recruitment and trial participation process and Table 1 outlines the outcome assessments used in this study, as well as the collection time points for the assessments. Participants will be asked to complete the relevant assessments online and an email reminder will be sent to each participant when the assessment is due, followed by a reminder one week later.

**Figure 2 figure2:**
[figure not shown]
Flow chart of recruitment and trial participation. RAPT: risk assessment and prediction tool; THA: total hip arthroplasty.

**Table 1 table1:** Summary of primary and secondary outcome assessments and collection time points used in the study.

Outcome assessment	Pre-admission	6 weeks postdischarge	3 months postdischarge	6 months postdischarge
HOOS^a^	✓	✓	✓	✓
EQ-5D-5L^b^	✓	✓	✓	✓
SEMCD^c^	✓	✓	✓	✓
Satisfaction survey		✓		
Web-based analytics^d^				✓

^a^HOOS: Hip Dysfunction and Osteoarthritis Outcome Score.

^b^EQ-5D-5L: EuroQol EQ-5D-5L.

^c^SEMCD: Self-Efficacy for Managing Chronic Disease.

^d^eHealth program only.

#### Primary Outcome

The primary outcome is patient-reported evaluation of symptoms and function limitations related to the affected hip (the hip undergoing surgery). The measure of this outcome is the Hip Dysfunction and Osteoarthritis Outcome Score (HOOS) version LK 2.0. The HOOS is a validated 40-item questionnaire where patients self-assess their hip across 5 subscales: (1) symptoms and stiffness, (2) pain, (3) function of daily living, (4) sports and recreational activities function, and (5) quality of life [15].

